#### At 3 months post-delivery

At 3 months post-delivery, the secondary outcomes are:EPDS scoreParenting stress.

See Additional file 4: Table S2 for further details of the measures and times of assessment.

## Measures

Data will be collected at the following time points: baseline, 14 weeks post-randomisation and 12 weeks post-delivery (see Additional file 4: Table S2 for a full list of the study measures). Baseline measures will be collected by researchers prior to the assignment of participants to the trial groups. Baseline interviews may take up to 45 minutes if women have been referred to the trial by clinic midwives or via self-referral; these women will need to undergo a detailed assessment of their eligibility for the trial. For women taking part in the related study, the interview will take between 5 and 8 minutes, as they will have already completed a detailed assessment of their eligibility for the trial and will just need to be asked some additional measures. The 14-weeks post-randomisation interview may take up to 30 minutes and the 3-months post-delivery interview up to 40 minutes. All follow-up measures will be collected by another researcher who will be blind to the allocation status of the participant. The researcher will ask the participant not to mention to which group she was allocated. A test of the success of masking will be carried out; at the end of each follow-up interview, the researcher will document his/her views on which arm of the trial he/she believes participants have been allocated to. At the end of the trial, we will compare the actual allocation status of participants against the researcher’s estimated allocation status to determine the strength of blinding in the trial.

The following data will be extracted from maternity records:Mode of delivery; maternal ethnicity; parity and pre-pregnancy body mass index (estimated at booking); fetal growth data as available from routine scansInfant outcomes: Apgar scores; birthweight; sex; gestational age to calculate customised birthweight centiles adjusted for maternal age; need for resuscitation; days in neonatal unit; growth weight and height centiles over first 12 weeks where available from routine measures in primary care.

The PWPs will also collect data using the PHQ-9 [28], GAD-7 [29], IAPT Phobia Scale [30] and IAPT Work and Social Adjustment Scale [31] at each session delivered to women in the Guided Self Help plus usual care group, as this is normal practice in all IAPT services.

### Process evaluation

A fidelity rating scale has been developed to rate adherence to the Guided Self Help components by the PWPs. We aim to audio-record five initial sessions for each PWP and rate their adherence to the intervention components using a checklist corresponding to the content of the workbook modules. Rating of fidelity will be carried out by two independent psychologists. Further ratings on a random sample of 20 sessions will ensure quality control and fidelity. The scale was designed to assess adherence to the key components of the intervention. It includes items such as setting an agenda/orienting the client to the session, discussing questionnaire scores, covering material from the workbook and reviewing and setting homework. It was necessary to use a slightly adapted version of the scale for the first and last sessions because of intrinsic differences (e.g. there was no homework to review from a previous session in the first session). Each item is rated according to its presence or absence from the session, with the item being scored if there was any evidence that it had been included. A rating of 80 % adherence indicates high fidelity.

Additionally, it was thought important to have a measure of the ability of the PWPs to develop a positive therapeutic alliance. Research suggests that the relationship between client and therapist is a key variable in relation to therapy outcomes ([32, 33], but see also [34]). The Cognitive Therapy Scale Revised (CTS-R) [35] is a widely used and well-validated instrument for evaluating therapist competency and adherence to CBT principles. It was not appropriate to use a full CTS-R, because the intervention was not full cognitive behaviour therapy but rather a cognitive behaviourally based Guided Self Help package. Item 5 of the scale concerns ’interpersonal effectiveness’ defined as ’the ability of the therapist to form a good relationship with the patient’. This includes the ability to put the client at ease, to facilitate disclosure of difficult material and to exhibit the nonspecific factors of empathy, genuineness and warmth delineated by Carl Rogers [36]. It was decided to use this item of the scale, rated from 0 to 6, as an indication of the extent to which PWPs were able to respond to their clients and build a positive therapeutic alliance. Scores on the scale should approximate to a normal distribution with a mid-point of 3, with very high scores reserved for expert competency, particularly in the face of difficulties. When the full scale is used, a mean score of 3 on each item is taken to indicate competency. Because the full scale could not be used, the ratings provide an indication of interpersonal effectiveness but do not represent the broader picture of CBT competencies assessed by the full scale. The PWP will also collect data on the mode of delivery of Guided Self Help sessions (i.e. face to face or via telephone).

Levels of compliance will be assessed using data collected by the PWPs on the number and length of Guided Self Help sessions offered and the number of sessions attended/not attended or cancelled.

Descriptions of treatment as usual will be recorded, including the frequency of contact with health/social care services (using the Adult Service Use Scale (AD-SUS)) at 14 weeks post-randomisation and 12 weeks post-delivery.

Qualitative data will be collected from interviews with a purposive sample (with respect to ethnicity, age and parity) of 20 women, after completion of the 3-months post-delivery research interviews. A brief topic guide will be used to ask participants for feedback about their expectations and experiences of participating in the intervention (and/or other care) and using maternity and primary care services.

## Sample size

This is primarily a feasibility trial, but we also carried out a sample size calculation to allow us to calculate what preliminary evidence we could generate on efficacy. Assuming a correlation of 0.4 between baseline and outcome EPDS symptom score, a two-arm parallel-group design with 52 women in each arm, the Stata procedure *sampsi* gives 79 % power to detect a difference of 0.5 SD using ANCOVA and a two-tailed test using a 95 % significance level (based on an effect size of 0.31, as this was found in a systematic review of Guided Self Help in non-maternity settings [22]). We aim to recruit 110 women. The study would have 66 % power to detect a difference in the caseness rate of recovery of 35 % in controls versus 60 % in the Guided Self Help arm.

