There are four specific main aims of this trial: (1) to establish that the trial procedures work (and fine-tune where necessary) so that a Phase III trial can follow; (2) to evaluate whether antenatal Guided Self Help is beneficial in improving depressive symptoms for women with antenatal depression; (3) to evaluate whether antenatal Guided Self Help has the added benefit of improving other outcomes, including post-treatment and post-delivery psychological symptoms, post-delivery bonding and quality of life; and (4) to explore whether antenatal Guided Self Help is likely to be cost-effective compared to usual care. The latter two aims will also estimate treatment effect sizes.

The following hypothesis will be tested:

Women with mild or moderate antenatal depression treated with Guided Self Help will have significantly lower Edinburgh Postnatal Depression Scale (EPDS) depressive symptoms at 14 weeks post-randomisation compared to women with mild or moderate antenatal depression receiving usual care.

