## Statistical analysis

Analysis will be by intention to treat; missing data will be imputed. The planned strategy for handling missing data at the item and scales will depend on the amount of missing data observed and the planned analyses for the outcomes. To ensure the same strategy is followed across all scales reported in the principle paper(s), any guidance given by authors of validated questionnaires will supersede the methods outlined herein.

If any of the baseline measures can be hypothesised to predict missing scale outcomes, it would be advantageous to include them in the modelling. To allow for this, any baseline measure considered as a covariate in the main modelling must be imputed to a full dataset. Missing baseline covariate item data will be imputed using mean imputation per participant (pro rating) or using the *ice* command in Stata to make a single imputation. There will be missing data in post-treatment outcome variables as participants are lost to follow-up. The regression analyses are based on maximum likelihood, and resulting inferences are valid provided the missing data generating mechanism is missing at random (MAR); that is, missingness is predicted only by variables that are included in the model, including earlier values of the outcome variable. We will empirically assess using logistic regression whether any baseline variables predict missingness, and should this be the case, we would condition on such variables by including them in the statistical model. Where post-randomisation variables predict missingness, we will make use of the MAR properties of (restricted) maximum likelihood random effects estimators for repeated measures.

Although the main aim of the trial is to assess feasibility, an exploratory primary outcome analysis will be carried out using a regression of the EPDS depression symptom score using baseline symptom score as a covariate (ANCOVA), with confidence intervals (CIs) calculated using bootstrap. Because the trial is embedded within a screening study, we will estimate the effect of the treatment on diagnostic rates of depression in the pregnant population using multiple imputation from EPDS symptom scores and screening scores available in the whole screened population.

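### The 79% power is for a difference of 0.5 SD, but the effect size of 0.31 given as its basis does not support that difference and corresponds to about 41% power

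*Protocol article*

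**What the plan says.** All the figures are in the Sample size section of the protocol article. It begins "Assuming a correlation of 0.4 between baseline and outcome EPDS symptom score" and takes 52 women per arm. It then says that the Stata procedure "gives 79 % power to detect a difference of 0.5 SD using ANCOVA", with "a two-tailed test using a 95 % significance level". A bracket closing the same sentence says that this is "based on an effect size of 0.31, as this was found in a systematic review of Guided Self Help in non-maternity settings". The next sentence sets the recruitment target: "We aim to recruit 110 women".

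Three other places bear on how this is read:

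- The Background section states the hypothesis that women given Guided Self Help "will have significantly lower Edinburgh Postnatal Depression Scale (EPDS) depressive symptoms at 14 weeks post-randomisation".
- The Sample size section calls the trial primarily a feasibility trial, and the Statistical analysis section calls the primary outcome analysis exploratory.
- The Statistical analysis section expects attrition: "There will be missing data in post-treatment outcome variables as participants are lost to follow-up".

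**The concern.** One sentence names two effect sizes as the foundation of one power figure. The power is computed at 0.5 SD. The evidence cited for it is 0.31, which is 38% smaller (1 - 0.31/0.5 = 0.38). The article does not explain why it powers for more than the cited evidence shows, and no step leads from one value to the other.

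What is at stake is interpretation. The section offers the calculation to show what preliminary efficacy evidence the trial can produce, and the hypothesis is worded in terms of significance. A reader who takes the 79% as resting on the review's effect may treat a non-significant EPDS comparison as evidence against an effect of that size. If the true effect were 0.31 SD, a non-significant result would be the more likely outcome.

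**Working it through.** **Inputs from the Sample size section:** 52 per arm analysed; correlation r = 0.4; ANCOVA; two-sided test; the 95% significance level read as alpha = 0.05; differences of 0.5 SD and 0.31. **Assumption:** 0.31 is a standardised mean difference, on the same scale as 0.5 SD.

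**Formulas** (outcome SD = 1)

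- SE = sqrt((1 - r²) × 2/n)
- Power = Φ(d/SE - 1.96)
- n per arm = 2 × (1.96 + z_power)² × (1 - r²)/d²

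**Step 1: reproduce the stated figure.** SE = sqrt(0.84 × 2/52) = 0.1797. At d = 0.5: 0.5/0.1797 - 1.96 = 0.822, so power = 79.4%. A noncentral t with 101 degrees of freedom gives 78.7%. The 79% reproduces, so 0.5 SD was the value entered.

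**Step 2: the cited effect with the same inputs.** At d = 0.31: 0.31/0.1797 - 1.96 = -0.235, so power = 40.7% (40.1% by noncentral t).

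**Step 3: all 110 women analysed, 55 per arm.** SE = sqrt(0.84 × 2/55) = 0.1748. At d = 0.31: 0.31/0.1748 - 1.96 = -0.186, so power = 42.6%.

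**Step 4: sample size for 80% power at 0.31.** 2 × (1.96 + 0.8416)² × 0.84/0.31² = 137.2, so 138 per arm. For 79% the figure is 134 per arm.

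**Step 5: could another reading make 0.31 give 79%?** With 52 per arm:

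| Reading at d = 0.31 | Power |
|---|---|
| ANCOVA, two-sided (as stated) | 40.7% |
| ANCOVA, one-sided | 53.2% |
| No baseline adjustment, two-sided | 35.2% |
| Change score, two-sided | 30.3% |
| ANCOVA, two-sided, r = 0.80 | 75.0% |
| ANCOVA, two-sided, r = 0.85 | 85.1% |

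Reaching 79% would need a correlation between 0.80 and 0.85, against the stated 0.4. If 0.31 were a correlation instead, the usual conversion gives d = 2 × 0.31/sqrt(1 - 0.31²) = 0.65, which is not 0.5 either.

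**Step 6: what the design can detect.** With 52 per arm, the difference detectable with 79% power is 0.497 SD, and with 80% power 0.504 SD. So 0.5 SD matches what the sample can detect.

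**Step 7: margin for losses.** 2 × 52 = 104 analysed out of 110 recruited leaves 6 losses, or 6/110 = 5.5%.

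**The case against.** The strongest reply is that no calculated figure is wrong. The sentence ties the 79% openly to 0.5 SD, so the detectable effect is not hidden. This stands: the fault lies in the stated basis and not in the arithmetic.

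A second reply is that the metric of 0.31 is not given. The Background section says the same review found benefit after treatment, limited benefit at long-term follow-up and variation across settings, and the article does not say which of these 0.31 describes. This also stands. A standardised mean difference is the natural reading, but the 41% depends on it. The missing link between 0.31 and 0.5 does not.

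A third reply is that the trial is primarily a feasibility study, its efficacy analysis is exploratory with bootstrap confidence intervals, and one objective is to estimate effect sizes. Nothing makes a Phase III trial depend on a significant result. This limits the consequence. It does not remove it, because the calculation is printed to inform readers about efficacy evidence and the hypothesis is still worded as a significance claim.

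A reader might go further in three ways that the article does not support:

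- **The sample is too small and should be raised to about 138 per arm.** A feasibility trial is not obliged to be powered for the review's effect.
- **A significance filter will carry an exaggerated effect into the economic decision model.** The Economic evaluation section makes the re-run depend on results that support the intervention, and it names no significance threshold.
- **Attrition will cut power to a particular lower figure.** The article gives no expected follow-up rate, and an attrition allowance may sit in the full protocol. Only the margin of 6 losses follows from its own numbers.

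**Conclusion.** The point holds as an internal contradiction of moderate severity. The 79% is right for 0.5 SD with 104 women analysed, but 0.31 is not a basis for it. Power at 0.31 is about 41% with 104 women analysed and 43% with 110, roughly half the printed figure. This rests on three readings: 0.31 as a standardised mean difference, the significance level as alpha = 0.05, and the stated correlation of 0.4. The absence of any link between 0.31 and 0.5 rests on none of them.

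**What to change.** In the Sample size section:

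1. Delete the bracketed statement that the calculation rests on 0.31.
2. State that 0.5 SD is the difference detectable with 79% power when 104 of the 110 recruited women are analysed, which leaves room for 6 losses. Alternatively, give a separate justification for 0.5 SD.
3. If 0.31 is kept as context, give its metric. If it is a standardised mean difference, report that power at that value is about 41%.
4. Add that, because efficacy is exploratory, the EPDS result will be interpreted from the estimated difference and its confidence interval, and that a non-significant result is not in itself evidence against an effect of 0.31.

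The cost is a few sentences. Recruitment, design and analysis do not change. The stated power simply becomes less favourable.

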## Statistical analysis

Analysis will be by intention to treat; missing data will be imputed. The planned strategy for handling missing data at the item and scales will depend on the amount of missing data observed and the planned analyses for the outcomes. To ensure the same strategy is followed across all scales reported in the principle paper(s), any guidance given by authors of validated questionnaires will supersede the methods outlined herein.

If any of the baseline measures can be hypothesised to predict missing scale outcomes, it would be advantageous to include them in the modelling. To allow for this, any baseline measure considered as a covariate in the main modelling must be imputed to a full dataset. Missing baseline covariate item data will be imputed using mean imputation per participant (pro rating) or using the *ice* command in Stata to make a single imputation. There will be missing data in post-treatment outcome variables as participants are lost to follow-up. The regression analyses are based on maximum likelihood, and resulting inferences are valid provided the missing data generating mechanism is missing at random (MAR); that is, missingness is predicted only by variables that are included in the model, including earlier values of the outcome variable. We will empirically assess using logistic regression whether any baseline variables predict missingness, and should this be the case, we would condition on such variables by including them in the statistical model. Where post-randomisation variables predict missingness, we will make use of the MAR properties of (restricted) maximum likelihood random effects estimators for repeated measures.

Although the main aim of the trial is to assess feasibility, an exploratory primary outcome analysis will be carried out using a regression of the EPDS depression symptom score using baseline symptom score as a covariate (ANCOVA), with confidence intervals (CIs) calculated using bootstrap. Because the trial is embedded within a screening study, we will estimate the effect of the treatment on diagnostic rates of depression in the pregnant population using multiple imputation from EPDS symptom scores and screening scores available in the whole screened population.

An odds ratio and 95 % CI for recovery, defined within IAPT as a PHQ-9 score of ≥10 at 14 weeks post-randomisation, will be estimated. We will compare groups for continuous scores on the EPDS at 14 weeks post-randomisation and 3 months post-delivery. The variance estimates will assist in power calculations for a definitive trial. Supplementary analyses will estimate complier average causal effects for a binary measure of compliance to treatment using the instrumental variable method. Therapist effects will be evaluated. Infant growth will be explored using random effects growth curve models (*xtmixed* in Stata) to compare birth and growth velocities of the groups.

Qualitative data will be coded in NVivo8 [37] following the principles of framework analysis [38], which includes the identification of a thematic framework, the abstraction and synthesis of key themes and the mapping and interpretation of the dataset as a whole. Qualitative results will be discussed within the context of quantitative data interpretation.

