## Methods/design

This study has been designed according to the Standard Protocol Items: Recommendations for Interventional Trials (SPIRIT) statement. Additional file 1: Table S1 presents the SPIRIT checklist, and Additional file 2: Figure S1 presents the SPIRIT figure for the schedule of enrolment, intervention and assessments.

The trial is a multi-centre Phase II exploratory randomised controlled trial with two parallel groups and a primary endpoint of EPDS depressive symptoms at 14 weeks post-randomisation.

Pregnant women with depression will be randomly allocated to either Guided Self Help plus usual care or to usual care alone (i.e. treatment as usual). Randomisation, stratified by type of depression (i.e. mild or moderate depression, or mixed anxiety and depression), will be performed using block randomisation of varying sizes with a 1:1 allocation.

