### Randomisation

Women will be randomly assigned to: (1) Guided Self Help (delivered by a Psychological Wellbeing Practitioner) plus usual care or (2) usual care alone (i.e. treatment as usual). Randomisation will be conducted independently of the trial investigators via the UK Clinical Research Collaboration (UKCRC) registered King’s Clinical Trials Unit bespoke web-based central randomisation service. Using a sampling fraction and cut-offs determined from the SCID instrument, collected during a related study on wellbeing in pregnancy (REC reference: 14/LO/0075), we will recruit women in three strata of mild or moderate depression or mixed anxiety depression. To ensure balance, the web-based central randomisation service will allocate women to trial groups (with a 1:1 allocation) using randomly varying blocks, stratified by severity of depression (assessed using scores on the SCID depression scale). The block sizes will not be disclosed, to ensure concealment.

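### The stated primary ANCOVA does not name the randomisation stratum; its interval is mildly conservative to the extent that the stratum predicts 14-week EPDS beyond baseline EPDS

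*Protocol article*

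**What the plan says.** On allocation, the Methods/design section of the protocol article says that randomisation is "stratified by type of depression (i.e. mild or moderate depression, or mixed anxiety and depression"). The Randomisation section says "we will recruit women in three strata of mild or moderate depression or mixed anxiety depression", that the central service "will allocate women to trial groups (with a 1:1 allocation) using randomly varying blocks", and that allocation is "stratified by severity of depression (assessed using scores on the SCID depression scale").

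On analysis, the Statistical analysis section calls the primary outcome analysis exploratory and specifies a "regression of the EPDS depression symptom score using baseline symptom score as a covariate (ANCOVA"), "with confidence intervals (CIs) calculated using bootstrap". The stratum is not mentioned in that section. The one stated route to further covariates is conditional: where baseline variables are found to predict missing outcomes, "we would condition on such variables by including them in the statistical model".

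**The concern.** Blocking within strata makes the two arms alike on the stratum, so between-stratum differences in outcome largely drop out of the true sampling error of the treatment effect. A model without the stratum still counts those differences as residual noise. If they are real, the standard error is too large and the interval too wide.

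The missingness rule is not a dependable remedy. It selects variables because they predict dropout, not because they governed allocation.

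Two stated uses of the results are affected. Estimating effect sizes is a listed objective, and the Statistical analysis section says that the variance estimates will inform the power calculation for a definitive trial. A residual variance that still contains stratum variation would carry into that calculation.

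There is also a labelling problem. One section calls the factor a type of depression and the other a severity, although one of the three groups is a diagnostic category and not a severity level. Whoever fits the model needs to know exactly which variable was used.

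**Working it through.** **Inputs from the Sample size section.** 52 women per arm, a difference of 0.5 SD, a baseline-outcome correlation of 0.4, a two-tailed test (5% level) and stated power of 79%.

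**Assumption, not in the article.** R² is the share of the variance left after baseline EPDS that the stratum explains. It is varied from 0 to 15%.

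**Step 1: reproduce the stated power.** The residual SD is √(1 − 0.4²) = √0.84 = 0.917. The standard error is 0.917 × √(2/52) = 0.180. Then 0.5/0.180 = 2.78, and Φ(2.78 − 1.96) = 79.4%. This matches the stated 79%, so the design calculation agrees with a model that has baseline EPDS as its only covariate.

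**Step 2: add the stratum by formula.** The residual SD becomes √(0.84 × (1 − R²)). The interval without the stratum is then 1/√(1 − R²) times as wide as the interval with it.

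**Step 3: check by simulation.** There were 6,000 trials per setting with 104 women, three strata of equal expected size, and allocation in blocks of 2, 4 or 6 within strata (assumed sizes, since the article withholds them). The correlation between stratum score and baseline EPDS was 0.5 (assumed). Intervals were model-based.

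| R² | Width ratio, formula | Power with stratum, formula | Width ratio, simulated | Coverage without / with stratum | Power without / with stratum, simulated |
|---|---|---|---|---|---|
| 0% | 1.000 | 79.4% | 0.998 | 94.8 / 94.9% | 78.5 / 78.4% |
| 2% | 1.010 | 80.2% | 1.009 | 95.2 / 95.0% | 78.4 / 79.0% |
| 5% | 1.026 | 81.4% | 1.024 | 95.4 / 95.1% | 79.2 / 80.7% |
| 10% | 1.054 | 83.5% | 1.053 | 96.0 / 95.2% | 79.4 / 82.3% |
| 15% | 1.085 | 85.5% | 1.083 | 96.3 / 95.3% | 80.1 / 85.0% |

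The Monte Carlo standard error of a coverage figure is about √(0.95 × 0.05/6,000) = 0.3 points.

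At R² = 15% the power forgone is 85.5 − 79.4 = 6.1 points by formula and about 5 points by simulation. The formula holds the comparator at 79.4%. In the simulation, blocking within strata also helps the model that omits the stratum.

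**Step 4: see where the loss falls.** At R² = 15%, the mean interval width without the stratum was 0.7149. This implies a standard error of 0.7149/(2 × 1.984) = 0.180, against a true sampling SD of 0.1685, so the model overstates it by about 7%. The estimator with the stratum had a sampling SD of 0.1652, and 0.1685/0.1652 = 1.02. The estimate itself loses only about 2%, and most of the cost is in the reported interval.

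**Step 5: check the bootstrap.** In a smaller run (300 trials, 200 resamples each), resampling individuals without regard to strata gave a standard error of about 0.179 at every R² tried. At R² = 20% the true sampling SD in that run was 0.160. The ordinary bootstrap therefore has the same excess width as the model-based interval.

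**Step 6: carry-over to a later trial.** Sample size is proportional to residual variance. If a definitive trial adjusts for the stratum but is sized on a variance that does not, it is too large by a factor of 1/(1 − R²): 1.00 at R² = 0 and 1/0.85 = 1.18 at 15%.

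**The case against.** The strongest reply is that a condensed article gives its model in one clause and never says that baseline EPDS is the sole covariate. It expects other covariates to be possible, does not fix the bootstrap scheme, and may have an analysis plan that lists the stratum. This stands as a limit: the point concerns the model as stated, not a proven omission from an unseen document. It does not remove the point, because the article does state its primary model and covariate, and its only route to more covariates is tied to missingness.

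Second, the size is small and uncertain. EPDS is itself a symptom-severity measure and may absorb much of what the stratum carries. At R² = 15% the stratum would add 0.15 × 0.84 = 12.6% of total variance, close to the 0.4² = 16% that baseline EPDS explains, so the top of the range is generous. This stands.

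Third, the stakes are modest. The analysis is labelled exploratory in a trial described as primarily a feasibility study, and the error is on the cautious side. This stands too.

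Fourth, the strata are mostly clear. The Randomisation section names three groups, and these match the diagnoses in the inclusion criteria. That answers most of the ambiguity under Methods/design. What remains is the word severity, which does not fit mixed anxiety and depression.

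Fifth, carrying the adjustment over to the PHQ-9 and GAD-7 proportions is not a neutral change. Odds ratios are non-collapsible, so adjusting for a prognostic factor changes the odds ratio being estimated. This is accepted, and the fix is limited accordingly.

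**Conclusion.** The point holds in a conditional form. The model as stated does not include the factor used in allocation, and adding it is good practice at almost no cost. For an assumed R² of 0 to 15%, the interval is about 0 to 8.5% wider than it would be with the stratum in the model, coverage is about 95 to 96.3%, and about 0 to 6 points of power are forgone. These figures also rest on 104 women analysed, a correlation of 0.4, and the assumed block sizes and stratum mix.

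A reader might infer three stronger conclusions, and the article supports none of them:

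- **That the interval is certainly too wide.** This needs the stratum to be prognostic beyond baseline EPDS. The article gives no figure for that, and at R² = 0 there is no loss.
- **That the result is biased or the type I error inflated.** Leaving out a balanced stratifier does not bias the treatment effect in a linear model, and the error it causes is conservative.
- **That the benefit of stratifying is thrown away.** Stratified allocation already gives most of the precision to the estimate. The reported interval does not reflect it.

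The mismatch between type and severity is real, but mainly a matter of wording.

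**What to change.** - **EPDS models.** Specify the regression of EPDS at 14 weeks on arm, baseline EPDS and randomisation stratum, with the stratum as a three-level fixed effect using the value entered in the randomisation system. Use the same covariates for EPDS post-delivery. If the analysis plan already does this, aligning the article's wording is enough.
- **Bootstrap.** Apply it to the model that contains the stratum. Resampling within arm and stratum is not a substitute for the fixed effect. In the small check it ran slightly narrow at R² = 20% (0.156 against 0.159).
- **PHQ-9 and GAD-7 proportions.** Adjustment is optional. If it is made, label the odds ratio as conditional on stratum.
- **Wording.** Describe the three strata in the same words under Methods/design and Randomisation, and drop the description of the factor as severity alone if it includes mixed anxiety and depression.

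The cost is two degrees of freedom and a few words. The variable was already collected for randomisation. If the stratum proves uninformative, the simulated loss of power is 0.1 point (78.5% to 78.4%), which is within simulation error.
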